### Study Type and Design

This study will be a crossover, 3-arm, randomized controlled trial. The protocol description followed the SPIRIT (Standard Protocol Items: Recommendations for Interventional Trial) [36] and the TiDieR (Template for Intervention Description and Replication) [37] guidelines (Figure 1 and Multimedia Appendices 1-4). Upon meeting eligibility criteria and agreeing to participate, participants will undergo an anthropometrics assessment, familiarization sessions, and strength assessment before randomly carrying out 3 separate experimental sessions (2 exercise and 1 control), with each session taking place over ~48 hours, over 3 consecutive days. The order of the sessions will be randomized and they will be separated by a minimum of 4 washout days.

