### Randomization and Blinding

After the fifth familiarization session, random allocation of the order of the experimental sessions’ participants will carry out will be performed as previously described [24-26]. The order in which the experimental sessions will be held will be randomized with the aid of the website. A collaborator not directly involved in any phase of the research (conceptualization, data collection and analysis, and reporting) will print the random orders generated by the program, insert them inside opaque, sequentially numbered envelopes, and seal them. After completing the fifth familiarization day, the envelope will be opened, and the sequence of experimental sessions will be revealed.

Due to characteristics inherent to this trial (resistance exercise), blinding of participants and researchers to exercise or control situations is not possible. However, participants and researchers will be blinded to CGM results (the blind model will be used). Furthermore, data and statistical analysis will be performed by a statistician blinded to groups and participants’ identities, as previously described [24-26].

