### Statistical Analysis

The sample size was calculated using data from relevant literature using similar individuals and glucose-assessing tools (CGM) [11,14,52,53]. Conservative parameters were inserted in the G*Power program (Heinrich-Heine-Universität Düsseldorf, version 3.1.9.6) for a repeated measure ANOVA within interaction: effect size of 0.2 (for 24-hour average glucose concentrations), probability of error type **α** of 0.05, power (probability of error type 1 β) of 0.95, correlation among repeated measurements of 0.7 [54], and nonsphericity correction of 0.5 [55,56]. With these parameters, 15 individuals are required (actual power of 0.96). Considering a typical dropout rate of 25% to 40%, we will initially recruit 25 participants.

A collaborator outside the research team will double-enter data coded for allocation into a computer in separate spreadsheets, allowing the researcher responsible for data analysis to assess the data without access to allocation information. Allocation will only be revealed after statistical analyses are run. In case of doubts about data entry (missing values or values outside the reference range), the researcher responsible for data analysis will contact the collaborator outside the research team responsible for double entry of the data to check accuracy. There will be no interim analysis.

To ensure confidentiality, all study-related information will be securely stored at the study site. All participant information will be kept in locked file cabinets in areas with access controlled by the principal investigator. All laboratory specimens, reports, data collection, process, and administrative forms will be identified by a coded ID number only to maintain participant confidentiality. Records containing names or other personal identifiers, such as locator forms and informed consent forms, will be stored separately from study records identified by code number. No personal information from participants will be released outside the study. Full access to the complete dataset will be restricted to members of the research team.

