The statistical analysis will follow the principles of intention-to-treat analysis [57]. Thus, data from participants will be assessed as randomized, regardless of whether they received the randomized treatment, meaning that even if they fail to follow the physical activity and diet instructions, or fail to complete the sessions as required, their data will be included in the analyses. Furthermore, we will also analyze the data “per protocol” [58], meaning that participants who deviate from instructions will be excluded from the final analyses. Differences in results stemming from intention-to-treat and per-protocol analyses will be discussed accordingly. The available variables will also be compared between participants who withdraw from the study and those who complete the study.

The effect of resistance exercise on glycemic control will be calculated as the absolute and percentage change between control and resistance exercise situations. Data will be expressed as mean and SD, with a 95% CI. For the analysis of data normality, we will perform the Shapiro-Wilk test. For normally distributed data, ANOVA will be used with 1 source of variation (experimental condition). If a significant main effect is observed, the post hoc Tukey test will be conducted. For nonnormal data, the Kruskal-Wallis test or Friedman test will be used as appropriate. The effect size will be calculated and interpreted as follows: <0.2=no effect, 0.2-0.49=low effect, 0.5-0.79=medium effect, and >0.8=large effect [59,60]. The significance level is set at 5%. The Prism program (version 10.1.1, GraphPad Software) will be used to generate graphs and analyze results. This trial will be reported following the CONSORT (Consolidated Standards of Reporting Trials) guidelines [61-63].

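### The stated condition tests (ANOVA with condition as the only source of variation, Kruskal-Wallis offered beside Friedman) do not match the three-condition crossover or the repeated-measures basis of the sample size

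*Protocol article*

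**What the plan says.** The Study Type and Design section of the protocol article sets the structure: "This study will be a crossover, 3-arm, randomized controlled trial". Every participant does a high-effort, a low-effort and a control session, and "The order of the sessions will be randomized and they will be separated by a minimum of 4 washout days".

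The sample-size paragraph under Statistical Analysis uses a repeated-measures ANOVA in G*Power with effect size 0.2, alpha 0.05, power 0.95, a correlation of 0.7 among repeated measurements and a "nonsphericity correction of 0.5". It arrives at 15 participants with actual power 0.96.

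Later in the same section, the tests are named. For normally distributed data, "ANOVA will be used with 1 source of variation (experimental condition" in parentheses. Then: "If a significant main effect is observed, the post hoc Tukey test will be conducted". Otherwise: "For nonnormal data, the Kruskal-Wallis test or Friedman test will be used as appropriate". The analysis text names no participant term, period term or sphericity correction.

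**The concern.** Three values from one person are correlated. An ANOVA in which condition is the only source of variation puts all between-person differences into the error term, as if there were three separate groups of 15. Kruskal-Wallis makes the same independence assumption, so it cannot be the right test for three conditions measured on the same people.

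The sample size takes credit for pairing and allows for nonsphericity. The stated analysis does neither. The mismatch therefore lies in what the document positively states, as well as in detail that a separate analysis plan might supply.

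The two possible readings err in opposite directions. Ignoring the participant makes the test far too conservative, and the Introduction hypothesizes that effort does not affect glycemic control. A near-powerless test would tend to return that result whatever the truth. Respecting the participant but ignoring nonsphericity makes the test too liberal.

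**Working it through.** **Inputs from the protocol article.** n = 15, three conditions (m = 3), correlation ρ = 0.7, nonsphericity ε = 0.5, effect size 0.2, alpha 0.05.

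**Assumptions.** The 0.2 is Cohen's f. The effect pattern is one condition differing from two equal ones: means of 0.424, 0 and 0 in SD units give f = 0.424 × √2 / 3 = 0.20.

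**The plan's own figure.** For a one-group repeated-measures ANOVA, λ = f² × N × m × ε / (1 − ρ), with degrees of freedom (m − 1)ε and (N − 1)(m − 1)ε. With m = 3 this does not give N = 15 at 95% power; it gives 41 at ε = 1 and 67 at ε = 0.5. N = 15 with power near 0.96 does appear under inputs that the article does not state, for example one group with about 31 measurements at ε = 0.5 (0.961). The numbers of groups and measurements are not reported, so this is a separate matter and is not counted as an error here.

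**Step 1. Standard error of a pairwise difference, in SD units.**
- Ignoring pairing: √(2/15) = 0.365.
- Paired: √(2 × (1 − 0.7)/15) = 0.200.
- Ratio: 1/√0.3 = 1.83.

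**Step 2. Power of the paired ANOVA at n = 15.**
- ε = 1: λ = 0.04 × 15 × 3 / 0.3 = 6.0, df 2 and 28, critical F 3.34, power 0.54.
- ε = 0.5: λ = 3.0, df 1 and 14, critical F 4.60, power 0.36.

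**Step 3. Literal tests against paired tests.** Simulation of 40,000 trials, ρ = 0.7, ε = 1:

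| Test | Type I error | Power at f = 0.2 |
|---|---|---|
| One-factor ANOVA, no participant term | 0.0005 | 0.051 |
| Repeated-measures ANOVA | 0.049 | 0.535 |
| Kruskal-Wallis | 0.0007 | 0.050 |
| Friedman | 0.047 | 0.403 |

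**Step 4. Paired ANOVA without a sphericity correction.** At ε = 0.5 the F ratio behaves approximately as F(1, 14) but is compared with the 5% point of F(2, 28), which is 3.34. P(F(1, 14) > 3.34) = 0.089. Simulation at other values:

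| ε | Uncorrected type I error | With Greenhouse-Geisser |
|---|---|---|
| 0.50 | 0.089 | 0.050 |
| 0.69 | 0.068 | 0.049 |
| 0.90 | 0.054 | 0.045 |

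**Step 5. No period term.** With an illustrative linear drift of 0.2 to 0.4 SD and unrestricted random order (both assumed), the type I error of the repeated-measures ANOVA stayed at 0.049 to 0.050. Power fell from 0.535 to between 0.525 and 0.481.

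**The case against.** The strongest reply is that the protocol means a paired analysis. The sample size is built on a repeated-measures ANOVA, and the exercise effect is defined as a change from the control session. The single source of variation may then be shorthand for a one-way repeated-measures ANOVA. This is plausible. If it is right, the 1.83-fold standard error and the 5% power do not apply. It does not explain why Kruskal-Wallis stands beside Friedman, and it leaves the sphericity question open.

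Friedman is named, and it blocks on participant. The section also plans to compare people who withdraw with those who complete, which is an independent-groups comparison. So "the Kruskal-Wallis test or Friedman test will be used as appropriate" does not commit the trial to Kruskal-Wallis for the crossover data. That stands: the defect is that Kruskal-Wallis is left available for the condition comparisons, with no rule that excludes it.

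A sphericity correction, a period term and the target of the normality check are often left to an analysis plan. This would carry weight if the article were silent throughout. It has weight for period and for normality. It has less for sphericity, because the sample-size paragraph itself assumes ε = 0.5 and the test description then carries no counterpart.

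The 8.9% is the extreme for three conditions. It should be read as an upper bound.

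A reader might also infer that leaving out period gives wrong standard errors or biased contrasts, and that the envelopes should be regenerated in blocks. The documents do not support this. Step 5 shows intact type I error and a modest loss of power under randomized order. Bias in a realized contrast needs a drift size, which the article does not give. On order generation it says only "The order in which the experimental sessions will be held will be randomized with the aid of the website" and refers to earlier publications for the method, so unrestricted randomization cannot be assumed.

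**Conclusion.** The point holds in this form: the tests as worded fit neither the crossover nor the sample-size basis, and either reading needs correction.

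- **Literal reading.** Pairing is lost: standard error 1.83 times too large, type I error below 0.1%, and power about 5% in place of about 54% (36% at ε = 0.5).
- **Charitable reading.** Pairing is kept. What remains is the unstated sphericity correction, with type I error up to 8.9% at ε = 0.5 and about 5% to 7% at milder departures.

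The power figures rest on 0.2 being Cohen's f and on the assumed effect pattern. The standard-error ratio needs only ρ = 0.7. It would go too far to say that the trial will certainly produce wrong standard errors: that depends on which reading the analyst follows, and Friedman is a valid option already in the text. The direction of harm also differs by outcome. An over-conservative test would favour the hypothesis of no glycemic difference between effort levels, but it would work against the predicted psychological differences and the anticipated benefit of exercise.

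**What to change.** Replace the sentence on the ANOVA with an explicit within-participant analysis. Either of these would do:

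- a linear mixed model with condition and period as fixed effects, participant as a random effect, and a covariance structure that allows nonsphericity; or
- a repeated-measures ANOVA with Greenhouse-Geisser correction.

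In addition:

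- Make the post hoc comparisons from within-participant differences.
- Check normality on model residuals. Raw values pooled over prediabetes and type 2 diabetes may be skewed between people even when the residuals are not.
- Keep Friedman, with paired follow-up tests, for clearly non-normal outcomes, and delete Kruskal-Wallis for the condition comparisons. If it is meant for withdrawers against completers, say so.

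The mixed model has the further advantage of using participants with incomplete sessions, which suits the intention-to-treat commitment and the expected dropout of 25% to 40%. The cost is a change of wording before analysis. The period term takes two degrees of freedom. No additional participants or measurements are needed for this change.

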More recently, attention has also been directed to the degree of effort during resistance exercise sets as a potentially important variable that can be manipulated to affect adaptative outcomes [27]. In fact, it has been suggested that a high degree of effort is important for acute improvements in glucose metabolism and insulin sensitivity in individuals living with T2D [28], although direct evidence of that is lacking. In our previous study [24-26], all sets were done with a high degree of effort (perceived exertion 9-10 out of 10 for all working sets). However, performing resistance exercise sets with a high degree of effort is associated with higher perceived exertion and discomfort [29], increased muscle soreness, negative psychological responses [30], and higher neuromuscular fatigue and muscle damage [31]. Taken together, these negative psychological and physiological responses to resistance exercise sets performed with a high degree of effort might negatively affect enjoyment and motivation during a resistance exercise session, which could ultimately reduce long-term adherence [32]. Individuals living with prediabetes and T2D might be more susceptible to these negative responses, as they are more physically inactive than the general population [33] and identify the lack of motivation and low self-efficacy (self-perception of the ability to accomplish something) as barriers to being more physically active [34].

Resistance exercise prescriptions should be tailored to meet not only the glycemic management needs of individuals living with prediabetes and T2D but also their motivation and self-perceived capacity to engage in exercise. Thus, the aim of this study is to assess the effects of the degree of effort during a resistance exercise session on glycemic control and psychological responses in individuals living with prediabetes and T2D. The hypothesis is that the degree of effort will not affect glycemic control, but that a high degree of effort will negatively affect psychological responses.

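### The High-versus-Low comparison and its confidence interval, which answer the effort question, are not assured, because the only named pairwise procedure runs after a significant three-condition omnibus test

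*Protocol article*

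**What the plan says.** All statements are in the protocol article.

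- **Aim.** The Introduction gives the hypothesis that "the degree of effort will not affect glycemic control, but that a high degree of effort will negatively affect psychological responses". For both halves of that sentence the relevant contrast is High against Low.
- **Omnibus test.** Under Statistical Analysis, for normally distributed data, "ANOVA will be used with 1 source of variation (experimental condition"). The conditions are High, Low and Control.
- **Gate.** "If a significant main effect is observed, the post hoc Tukey test will be conducted". No other pairwise procedure is named.
- **Non-normal branch.** "For nonnormal data, the Kruskal-Wallis test or Friedman test will be used as appropriate". No pairwise follow-up is named here, even after a significant result.
- **Reported without a gate.** The absolute and percentage changes of exercise against Control, summaries as mean and SD with a 95% CI, and effect sizes. A High-Low difference is not among the named estimates.
- **Sample size.** 15 participants, 25 recruited, "effect size of 0.2 (for 24-hour average glucose concentrations"), "correlation among repeated measurements of 0.7", nonsphericity correction 0.5, target power 0.95, stated actual power 0.96.

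**The concern.** The trial asks about one specific contrast, but the plan reaches it only through a global test that mixes effort with exercise versus no exercise. If the global test is not significant, the rule stops there and plans no pairwise comparison.

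This matters more here than in a trial that hopes to show a difference. The investigators expect High and Low to be alike for glycemic control. To judge that, a reader needs the High-Low difference with its confidence interval, to see how large a difference remains compatible with the data. As written, the plan does not assure this interval in the trials where the global p-value is unremarkable. A non-significant global test cannot stand in for it.

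This is a stated decision rule, not a detail left to another document.

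**Working it through.** **Inputs.** From the sample-size paragraph: n = 15 (or 25 if every recruit completes), effect size 0.2, correlation ρ = 0.7, ε = 0.5, α = 0.05. From the design: m = 3 conditions. Assumptions: 0.2 is Cohen's f (the usual ANOVA input), the ANOVA is paired, and the SD is 1 in each condition. Sphericity (ε = 1) is shown alongside the protocol's 0.5.

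**The plan's own figure.** With λ = f²·n·m·ε/(1−ρ) and df = (m−1)ε and (n−1)(m−1)ε, the stated power of 0.96 at n = 15 does not reproduce for a three-condition test. It is recovered only with many more repeated measurements than three, for example about 29 to 32 in one group at ε = 0.5. The protocol does not give the number of measurements used, and it names an interaction test rather than the one-factor test planned. So 0.96 cannot be taken as the chance of passing the gate.

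**How often the gate closes.**

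| n | ε | λ | df | Critical F | Omnibus power | No pairwise test |
|---|---|---|---|---|---|---|
| 15 | 1 | 0.04×15×3×1/0.3 = 6.0 | 2, 28 | 3.34 | 0.536 | 46% |
| 15 | 0.5 | 3.0 | 1, 14 | 4.60 | 0.365 | 64% |
| 25 | 1 | 10.0 | 2, 48 | 3.19 | 0.789 | 21% |
| 25 | 0.5 | 5.0 | 1, 24 | 4.26 | 0.574 | 43% |

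With no true effect of any kind, the gate closes in 95% of trials, which is simply 1 − α.

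**Does the gate protect error control?** Simulation at n = 15, ρ = 0.7, no true effect: at least one false-positive Tukey comparison in about 5.0% of trials without the gate and 4.5% with it. Tukey alone holds the 5% level.

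**Does the gate cost power?** Simulation at n = 15, f = 0.2, sphericity:

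| True pattern | Comparison | Tukey ungated | Tukey gated |
|---|---|---|---|
| Only High differs | High-Low | 37.6% | 36.9% |
| Low midway between Control and High | High-Low | 12.3% | 12.2% |
| Both exercise sessions differ equally from Control | High-Control | 37.7% | 37.0% |

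The loss is under 1 point in each row. In the midway pattern the widest pair, High-Control, loses a little more (49.9% to 48.3%).

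**What the missing interval would look like.** The SD of a paired difference is √(2(1−0.7)) = √0.6, so its standard error at n = 15 is √(0.6/15) = 0.20 SD.

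- Unadjusted half-width: t(0.975; 14) × 0.20 = 2.145 × 0.20 = 0.43 SD.
- Tukey-adjusted half-width: q(0.95; 3, 28)/√2 × 0.20 = 3.499/1.414 × 0.20 = 0.49 SD.

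**Can a reader rebuild it from the ungated output?** The point difference, yes. The interval, no: intervals around condition means do not carry the within-person correlation. Ignoring it gives a standard error of √(2/15) = 0.37 SD in place of 0.20 SD.

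**The case against.** An omnibus test followed by Tukey is a conventional sequence that controls error and is slightly conservative here. The gate costs almost no power: most trials in which it closes would have shown no significant Tukey comparison anyway. The frequency of a closed gate therefore mainly reflects low omnibus power, which is a sample-size matter. Condition means with 95% CI, effect sizes and exercise-versus-Control changes are reported regardless, and the High-minus-Low point difference follows by subtraction. An analysis plan not shown might also list the contrasts.

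Much of this stands, and it rules out three stronger readings that a reader might infer.

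- *That the gate seriously weakens the tests.* The simulations do not support this. A single planned contrast pooling both exercise sessions against Control would have more power, but it answers another question and says nothing about effort.
- *That nearly half of trials would have no pairwise test.* This holds only at n = 15 under sphericity. The protocol's inputs and recruitment target give 21% to 64%.
- *That a closed gate leaves only a global p-value as evidence on effort.* The ungated summaries contradict this.

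What the objection does not remove is that none of the ungated output is the paired High-Low interval. An unseen analysis plan could add it, but the article's rule as stated makes pairwise comparison conditional.

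**Conclusion.** The point holds in a narrow form. The gate is redundant for error control and nearly harmless for power. Its real consequence is that the High-Low comparison and its interval are not assured when the omnibus test is non-significant. At the protocol's effect size and correlation, that is 46% (ε = 1) to 64% (ε = 0.5) of trials with 15 completers, and 21% to 43% with 25. These figures rest on reading 0.2 as Cohen's f, on a paired ANOVA and on equal SDs across conditions.

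The planned inference is not invalid. It would also be wrong to infer that removing the gate lets a non-significant High-Low test confirm the hypothesis: such a test, gated or not, does not show that the two sessions are alike. The conclusion should rest on the interval, which at n = 15 would span about ±0.49 SD with Tukey adjustment, or ±0.43 SD without.

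**What to change.** In Statistical Analysis, replace the conditional Tukey sentence with:

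> The High-Low, High-Control and Low-Control paired differences are pre-specified and always reported with 95% CI, whatever the omnibus p-value; Tukey adjustment is applied directly to the three comparisons. High-Low is the contrast that addresses degree of effort.

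Add that any statement that effort makes no difference to glycemic control will be based on the High-Low interval and not on a non-significant p-value. Say that the same three differences are reported when the non-parametric branch is used.

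The cost is wording only: no new data, no more participants, and family-wise error stays at about 5%.

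### Calling a point estimate below 0.2 'no effect' is unsound with about 15 participants and favours the trial's own hypothesis of no difference by effort

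*Protocol article*

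**What the plan says.** The relevant text is in the Statistical Analysis section of the protocol article.

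- **Interpretation rule.** An effect size will be calculated and read against fixed bands: "<0.2=no effect, 0.2-0.49=low effect, 0.5-0.79=medium effect, and >0.8=large effect". A value of exactly 0.2 is in the low band; only values strictly below 0.2 are called no effect. The index and the contrast are not named. The cut-offs 0.2, 0.5 and 0.8 are those customary for a standardized mean difference.
- **Other reporting.** The same paragraph plans absolute and percentage changes between the control and exercise sessions, means and SDs with 95% CIs, a one-factor ANOVA over conditions and a post hoc Tukey test. On error rate it says "The significance level is set at 5" percent.
- **Sizing.** The sample size was computed "for a repeated measure ANOVA within interaction", with "effect size of 0.2 (for 24-hour average glucose concentrations"), "correlation among repeated measurements of 0.7" and "nonsphericity correction of 0.5". The result is "15 individuals are required (actual power of 0.96"). Recruitment is 25, to allow for 25% to 40% dropout.
- **Hypothesis.** The last paragraph of the Introduction expects effort to make no difference to glycemic control. The Discussion repeats that expectation.

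**The concern.** A point estimate near zero can come from a true difference near zero or from an imprecise estimate of a difference that matters. A rule that labels the estimate 'no effect' whenever it is below 0.2 does not separate the two, because it ignores the standard error. In most superiority trials this would be a loose choice of word. Here it bears on the main claim: the investigators expect the high- and low-effort sessions to have the same glycemic effect, and 'no effect' is the label that seems to confirm it. A report could combine a non-significant test with a 'no effect' label and conclude that effort does not matter, when the data would also fit a moderate difference.

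**Working it through.** **1. The plan's own figure.** The article does not state how many groups and measurements were entered. Assuming 3 groups and 48 measurements, with f = 0.2, correlation 0.7 and correction 0.5:

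- λ = f² × N × m × ε / (1 − ρ) = 0.04 × 15 × 48 × 0.5 / 0.3 = 48
- df1 = (3 − 1)(48 − 1)(0.5) = 47; df2 = (15 − 3)(48 − 1)(0.5) = 282
- power at 5% = 0.956, which rounds to the stated 0.96.

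So the 0.2 behaves as Cohen's f for an interaction. Recruitment of 25 at 40% dropout gives 25 × 0.60 = 15 completers.

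**2. Inputs for the check.** n = 15 and ρ = 0.7 are from the Statistical Analysis section. Assumed: equal variances in the sessions, normal data, and the index d = mean high-minus-low difference divided by the between-person SD. The true differences of 0.3 SD and 0.42 SD are illustrations; neither is a target that the plan sets.

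**3. Standard error of d.** With the SD treated as known:

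- SE = √(2(1 − ρ)/n) = √(0.6/15) = √0.04 = 0.20.

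Estimating the SD from 15 people adds a little, giving about 0.21 to 0.22 for small differences. One standard error is therefore as wide as the distance from zero to the 'no effect' limit.

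**4. Probability of the 'no effect' label.** P(|d̂| < 0.2) = Φ((0.2 − d)/SE) − Φ((−0.2 − d)/SE), with SE = 0.20:

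| True difference | Calculation | Probability |
|---|---|---|
| 0.3 SD | Φ(−0.5) − Φ(−2.5) = 0.309 − 0.006 | 0.30 |
| 0.42 SD | Φ(−1.1) − Φ(−3.1) = 0.136 − 0.001 | 0.13 |
| 0 | Φ(1) − Φ(−1) | 0.68 |

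Simulation with the SD estimated gives 0.30, 0.13 to 0.14 and 0.67. Standardizing by the control-session SD or by the pooled SD makes no material difference.

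**5. What an estimate in the band is compatible with.** The 95% half-width is about t(14) × SE = 2.145 × 0.20 = 0.43. An estimate just under 0.2 has an interval from about −0.23 to 0.63, which reaches into the article's own medium band.

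**6. Sensitivity, at a true 0.3 SD.**

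- ρ = 0.5: SE = √(1/15) = 0.258, probability 0.32.
- ρ = 0.9: SE = √(0.2/15) = 0.115, probability 0.19.
- 18 completers (25% dropout from 25 leaves 18.75), ρ = 0.7: SE = √(0.6/18) = 0.183, probability 0.29.
- Index standardized by the SD of the paired differences: 0.3/√0.6 = 0.387, SE about 1/√15 = 0.258, probability about 0.22.

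The size varies, but the label stays common for a real difference in all of these.

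**The case against.** **The label is only descriptive.** The article also plans tests, CIs and raw changes, and nowhere says that a conclusion of no difference will rest on the label. Nor does the banding cause the scatter: a true 0.3 SD sometimes estimated below 0.2 is ordinary sampling error with 15 people. Both statements are correct, so it would be too strong to say that the rule gives the expected answer by construction. What remains is that the article chooses the words 'no effect' for an estimate that cannot bear them, on the question where the expected answer is no effect.

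**The index is left to a fuller document.** Not naming it is detail that an article may leave out, and that omission is not the point here. The stated rule is the problem.

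**A stronger reading is tempting.** A reader might infer that, because the trial is sized on 0.2 and 'no effect' lies below 0.2, the planned effect would itself be called no effect. The documents do not support this.

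- The value 0.2 falls in the low band as written.
- If f = 0.2 is treated as a three-condition main effect, the largest pairwise difference is 0.2 × 3/√2 = 0.42 when one condition differs, or 0.2 × √6 = 0.49 when the means are evenly spaced. Both are also low.
- Applying the bands to an estimated f, with the true f at 0.2, puts about 41% of trials below the cut-off. That comes mainly from placing the truth on the cut-off, and the bands read more naturally as mean-difference bands.
- The sizing was for an interaction, which has no direct pairwise equivalent, so 0.42 to 0.49 cannot be taken as the planned effect.

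**Conclusion.** The concern holds for the interpretation rule alone. Reading any effect size below 0.2 as no effect is unsound at this sample size: the standard error is about 0.21, and a true high-versus-low difference of 0.3 SD gets the label in about 30% of trials (about 13% at 0.42 SD). These figures assume 15 completers, correlation 0.7, equal variances, normal data and a pairwise difference standardized by the between-person SD. Under the other correlations, completer number and standardizer tried, the 30% ranges from 19% to 32%. Because the hypothesis is one of no difference by effort, the error runs in the direction of the expected answer. The conclusion does not extend to the sizing effect, which the bands do not classify as no effect.

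**What to change.** In the interpretation sentence of the Statistical Analysis section:

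- apply the 0.2/0.5/0.8 bands to the pairwise standardized mean difference, including the high- versus low-effort contrast, and report each with its 95% CI;
- replace the 'no effect' label for values below 0.2 with 'trivial point estimate';
- state that neither this label nor a non-significant test is evidence of no difference, and that any conclusion of no difference will rest on the CI.

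Do not write 0.42 to 0.49 into the sample-size paragraph as an equivalent of the 0.2; that conversion holds only for a three-condition main effect.

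The cost is a few sentences, with no change to design, data or sample size. The real price is that the trial can claim less from a small point estimate: with a half-width near 0.43, a result close to zero may have to be reported as inconclusive about effort.
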